#### Secondary outcomes

##### Proportions

Secondary outcomes on binary scale include the proportion of children (1) with OM or hearing loss who receive a case management plan, (2) with a diagnosis requiring follow-up who receive an ear assessment within 10 days, (3) who receive screening otoscopy, (4) who receive screening tympanometry or pneumatic otoscopy, (5) 5 to 16 years of age who receive hearScreen, and (6) < 5 years of who receive parent listening and understanding measure and hearing and talking score (PLUM and HATS) assessments. For these outcomes, the approach applied to the primary outcome will be employed—estimates of treatment effect will be presented as odds ratios and 95%CI following a multilevel mixed-effects generalised linear regression model.

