## Objectives

The aim of the HfLI is to improve the ear and hearing health of Aboriginal children living in the Northern Territory.

Our primary hypothesis is that implementation of the HfLI model of health service facilitation will increase ear and hearing health surveillance (documented in the medical records) among children 0 to 16 years of age. Our secondary hypotheses are that compared to control periods; the HfLI will improve evidence-based management of OM and hearing loss, improve access to specialist services, improve follow-up care, reduce the prevalence and severity of OM and hearing loss and improve family and children’s quality of life, school attendance and performance. We also hypothesise that the co-design and delivery of training and employment on country has benefits for the Ear Health Trainees, the Ear Health Facilitators, families and professional health and education staff, including the opportunities this model might provide for training and employment in other health areas, and other service sectors of importance to their community.

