#### Secondary outcomes—ear and hearing observations and presumptive diagnoses (in the last 6 months)

For the resident population of 0- to 16-year-old children, we will report the proportion who have had the following: an ear observation attempted; otoscopy, tympanometry or both; a presumptive diagnosis; a clinical diagnosis; and a documented management plan.

For the resident population of 0- to 5-year-old children, we will report the proportion completing parental questionnaires. For the resident population of 5- to 16-year-old children, we will report the proportion with the following: hearScreen tests completed, presumptive hearing loss documented, an appropriate documented management plan and an appropriate documented referral for each specialist service.

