##### Subgroup analyses

There may be possibilities of differences in characteristics of populations across the 18 communities during the study period that may confound with the effect of the HfLI. In subgroup analysis, we will adjust for age, sex and factors associated with socio-economic disadvantage in Indigenous children. The subgroup analysis will be carried out as either a stratified analysis or inclusion of an interaction term between each subgroup variable, HfLI factor and time. In all analysis, statistical significance will be set at 5% significance level (*p* < 0.05). Analysis will be conducted using Stata 15.1 (StataCorp LLC, College Station, TX, USA).

The analysis population will be children 0 to 16 years of age who are resident in the participating community. The proportion of the population that receive services will be reported. There will be no imputation for those not seen. We will report participant flow (clusters and participants) for control and HfLI periods, the number of clusters and participants who were assessed for eligibility, were randomly assigned, received intended treatment, and were analysed for the primary outcome.

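### Management-plan and 10-day follow-up odds ratios are computed among diagnosed children, a group HfLI is meant to enlarge, so randomisation does not protect them; for plans, the denominator also differs between sections

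*Protocol article*

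**What the plan says.** Under Statistical methods, the Proportions section lists six binary secondary outcomes. The first two have a denominator defined by disease or diagnosis: children "with OM or hearing loss who receive a case management plan", and children "with a diagnosis requiring follow-up who receive an ear assessment within 10 days". For all six, "the approach applied to the primary outcome will be employed", which means a mixed logistic model with the result presented as a treatment-effect odds ratio.

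The outcome section on ear and hearing observations and presumptive diagnoses sets a different base: "For the resident population of 0- to 16-year-old children, we will report the proportion who have had the following". Its list ends with "a clinical diagnosis; and a documented management plan". The 10-day follow-up outcome is not in that list.

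The Subgroup analyses section states: "The analysis population will be children 0 to 16 years of age who are resident in the participating community". It adds: "There will be no imputation for those not seen".

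The primary hypothesis in Objectives is that HfLI "will increase ear and hearing health surveillance (documented in the medical records) among children 0 to 16 years of age". The Primary outcome section under Statistical methods equates an ear assessment with a diagnosis.

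**The concern.** The data come from medical records. A child counts as having OM, hearing loss or a diagnosis needing follow-up only if someone assessed the child and recorded the result. HfLI is expected to change how many children, and which children, meet that condition. Both denominators are thus formed by something the intervention acts on after a community crosses over. The two groups of diagnosed children need not be alike, even though the communities were randomised to their start dates.

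The Background argues that selection bias is low because age is the only entry criterion for children. That holds for residents. It does not hold for a group that must also have a recorded diagnosis.

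At stake are the secondary hypotheses on evidence-based management and follow-up. An odds ratio among diagnosed children mixes any change in care with any change in who is diagnosed. It could be read as no benefit, or as harm, while more children receive a plan. For plans there is a second problem: the article supports two denominators and does not say which one carries the effect estimate.

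**Working it through.** The article gives no rates or effect sizes for these two outcomes, so there is no stated figure to reproduce. The check uses the protocol's planned change in assessment plus assumed rates.

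**From the Sample size section:** control proportion assessed 0.329; absolute increase 0.10, giving 0.429.

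**Assumed:** the children assessed under control would also be assessed under HfLI, with the same plan rate. OM is present in 80% of them and in 50% of the added children. The plan rate is 80% in existing cases; in added cases it varies.

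**Formulas, per 1,000 residents:**
- Existing cases D0 = 1000 × 0.329 × 0.80 = 263.2
- Added cases Dn = 1000 × 0.10 × 0.50 = 50
- Cases under HfLI = 263.2 + 50 = 313.2, of which 50/313.2 = 16% are newly found
- Plans under control = 263.2 × 0.80 = 210.56
- Plans under HfLI = 210.56 + 50 × rn, where rn is the plan rate in added cases
- Conditional proportion = plans / cases; resident proportion = plans / 1000
- OR = odds under HfLI / odds under control

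**With rn = 0.60:** plans = 210.56 + 30 = 240.56.
- Conditional: 240.56/313.2 = 76.8%, against 80.0%. OR = (0.768/0.232)/(0.80/0.20) = 3.31/4 = 0.83.
- Resident: 24.1%, against 21.1%. OR = (240.56/759.44)/(210.56/789.44) = 0.3168/0.2667 = 1.19.

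**Varying rn:**

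| Plan rate in added cases | Plans under HfLI | Conditional proportion (control 80.0%) | Conditional OR | Resident proportion (control 21.1%) | Resident OR |
|---|---|---|---|---|---|
| 60% | 240.56 | 76.8% | 0.83 | 24.1% | 1.19 |
| 80% | 250.56 | 80.0% | 1.00 | 25.1% | 1.25 |
| 90% | 255.56 | 81.6% | 1.11 | 25.6% | 1.29 |

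**Other assumed yields.** Suppose 70% of all assessed children have OM, borrowing the prevalence that the Background gives for young children. Cases then go from 230.3 to 300.3, so 23% are newly found. Plan rates of 90% (existing) and 60% (added) give a conditional OR of 0.54 and a resident OR of 1.27. Rates of 90% and 90% give 1.00 and 1.42.

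**General condition.** With management of existing cases unchanged, the conditional proportion falls whenever rn is below the existing rate. The resident proportion rises whenever rn is above zero. Between those limits the two odds ratios lie on opposite sides of 1. The same algebra applies to 10-day reassessment, with reassessed in place of given a plan.

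**The case against.** The strongest counter-argument is that the hypothesis concerns how well children with disease are managed, so the proportion among diagnosed children is the natural quality-of-care measure. A resident proportion rises with detection alone: in the 90%/90% case above its OR is 1.42 although management has not changed. Used alone, it would partly restate the primary outcome. This stands, and it is why the conditional figure should be kept.

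It can also be said that the two plan denominators may coexist, one as coverage and one as quality. That is fair for reporting. But the article attaches an effect estimate only to the conditional version, and it names residents as the analysis population.

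A reader might infer more than the documents support:
- **That HfLI adds milder cases while control cases are mostly children who presented.** Table 4 lists school screening within usual care and says priority children under HfLI are chosen by the service and the OM Guidelines. Severity is not documented in either direction.
- **That the odds ratio will reverse.** This needs added cases to get plans less often than existing ones. The Management plan section makes a health professional responsible for both diagnosis and plan after an abnormal finding, and facilitators help with care plans and follow-up appointments. Added cases could be managed as well or better.
- **That the distortion is larger.** Taking Table 4's target of 100 children screened in an assumed community of 250, and supposing 32.9% of them would have been assessed anyway, about 67 children are added. The ORs become 0.68 and 1.54. That is a rise of about 27 points, against the 10 points on which the trial is planned.
- **That the denominators conflict for both outcomes.** The outcome section lists plans only. The 10-day outcome shares the selection problem and the mismatch with the analysis population.

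**Conclusion.** The point holds in limited form. Two secondary outcomes are given treatment-effect odds ratios within groups whose membership depends on assessment and diagnosis, which HfLI is intended to increase. Those comparisons are not protected by randomisation, and the article does not address this. For management plans the denominator also differs between the outcome section and the Proportions section.

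The direction of bias is unknown. At the protocol's 10-point rise, the assumed rates give a conditional OR from 0.83 to 1.11 while the resident OR runs from 1.19 to 1.29. The OM yields, the plan rates and the unchanged management of existing cases are all assumptions, because the article gives no values. The documents do not support saying that HfLI will appear harmful on these outcomes, only that the conditional odds ratio cannot tell a change in care from a change in who is diagnosed. The primary analysis is unaffected.

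**What to change.** - For both outcomes, make the proportion of all residents in each period the randomised effect estimate: child diagnosed and given a plan; child diagnosed and reassessed within 10 days. State that it combines detection and management.
- Keep the proportion among diagnosed children beside it as a quality-of-care measure, labelled as conditional on a diagnosis made after crossover and not a causal effect.
- Reconcile the outcome section, the Proportions section and the analysis-population statement in Subgroup analyses, so that each outcome has one stated denominator for its effect estimate.

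The cost is wording, since the records of all resident children are already to be extracted. The drawback is that the resident measure partly overlaps the primary outcome, so the two figures must be read together.

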##### Rates

Episodes of AOM, OME, AOMwiP, CSOM or DP over the trial period will be summarised as counts according to treatment groups. The effect of the HfLI will be determined using multilevel mixed-effects negative binomial regression expressed as incidence rate ratio (IRR) and the 95% CI. Time will be fitted as a categorical fixed effect and random coefficient and random intercept for cluster. The same approach will be followed to estimate the treatment effect on rate of appropriate use of antibiotics for (1) persistent otitis media with effusion (pOME), (2) AOM without perforation, (3) AOM with perforation, (4) CSOM (topical) in the last 6 months, (5) rate of appropriate specialist referral (audiology), and (6) rate of appropriate specialist referral (ENT).

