#### Trial phase

Data from all 18 participating communities (PCIS and Communicare) for the period from the start to the end of the trial will be retrieved 6-monthly using the data-identity separation principles for data retrieval and data linkage.

Ear assessment data entered and retrieved from the PCIS or Communicare systems by all health professionals and by Ear Health Facilitators will contribute to the analyses. Data collected by the Ear Health Facilitators alone (paper-based forms or tablets (REDCap) can be used to determine the contributions by the Ear Health Facilitators.

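### The incidence rate ratio for recorded otitis media episodes mixes detection with disease, so it cannot test whether otitis media falls under HfLI

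*Protocol article*

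**What the plan says.** All references are to the protocol article.

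- **Rates (secondary outcomes).** "Episodes of AOM, OME, AOMwiP, CSOM or DP over the trial period will be summarised as counts according to treatment groups". The HfLI effect comes from a multilevel negative binomial model, with an incidence rate ratio and 95% CI. For antibiotics and specialist referral: "The same approach will be followed to estimate the treatment effect on rate of appropriate use of antibiotics". No denominator is named for either group of outcomes.
- **Subgroup analyses, second paragraph.** "The analysis population will be children 0 to 16 years of age who are resident in the participating community". Also: "There will be no imputation for those not seen".
- **Trial phase (data collection).** "Ear assessment data entered and retrieved from the PCIS or Communicare systems by all health professionals and by Ear Health Facilitators will contribute". Episodes therefore come from routine records that include Facilitator entries.
- **Objectives.** The primary hypothesis is that HfLI "will increase ear and hearing health surveillance (documented in the medical records) among children 0 to 16 years of age". A secondary hypothesis is that it will "reduce the prevalence and severity of OM and hearing loss".
- **Table 4, item 8.** Facilitators are to screen at least 100 children per community in each 6-month period.

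**The concern.** An unexamined child contributes no episodes, whatever the state of the ears. Examination is what the intervention sets out to increase, so HfLI status changes how the outcome is ascertained. Adjustment for calendar period does not remove this, because ascertainment changes with HfLI status itself.

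The resulting ratio is the product of a detection effect and any disease effect. If HfLI succeeds on its primary outcome, the detection part pushes the episode IRR upwards, against the stated hypothesis of less otitis media. Called an incidence rate ratio, it invites a reader to see harm, or to miss a benefit. Counts of appropriate antibiotic use and referral per resident would rise for the same reason, and there the rise would look like better care.

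**Working it through.** **The plan's own figure.** The protocol gives no figure for the rate outcomes. The planning values used here come from Sample size: control proportion 0.329, absolute increase 0.10, 18 communities, 90 children per community and period. The stated total reproduces: 18 × 90 = 1620. With ICC 0.06, CAC 0.7, sequences 2:4:4:4:4 and 7 periods, a linear mixed-model calculation gives power of 96.1% to 99.5% for individual autocorrelation from 0 to 0.9, against the stated 98%. This check only confirms that the inputs are read correctly.

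**Inputs for the detection effect**
- p0 = 0.329 and p1 = 0.329 + 0.10 = 0.429, the proportions of residents assessed in a period (Sample size).
- y = episodes per additionally examined child, relative to a child who would have been examined anyway. The protocol does not give it. Assumed range: 0.25 to 1.
- d = true disease ratio; d = 1 means disease unchanged.

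**Formulas**
- Recorded-episode IRR per resident = d × [1 + y(p1 − p0)/p0].
- Ratio per examined child with d = 1: [p0 + y(p1 − p0)]/p1.

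At y = 0.5 the first is 1 + 0.5 × 0.10/0.329 = 1.15 and the second is 0.379/0.429 = 0.88.

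| y | IRR per resident, d = 1 | True fall needed to bring the IRR to 1.0 | IRR if disease truly falls 20% | Ratio per examined child, d = 1 |
|---|---|---|---|---|
| 1 | 1.30 | 23% | 1.04 | 1.00 |
| 0.75 | 1.23 | 19% | 0.98 | 0.94 |
| 0.5 | 1.15 | 13% | 0.92 | 0.88 |
| 0.25 | 1.08 | 7% | 0.86 | 0.83 |

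The third column is 1 − 1/IRR and the fourth is 0.8 × IRR, both computed from unrounded values.

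Over the protocol's own sensitivity ranges (baseline 0.23 to 0.53, increase 0.10 to 0.20) with y = 1, the detection-only IRR runs from 0.63/0.53 = 1.19 to 0.43/0.23 = 1.87.

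**Simulation check.** 18 clusters, 7 periods, 100 residents per cluster, true incidence unchanged, 300 replicates. The model was quasi-Poisson with cluster and period fixed effects, a stand-in for the planned negative binomial mixed model. The variance components, 0.7 episodes per examined child and y are assumptions.

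| Analysis | y = 1: mean IRR (p < 0.05) | y = 0.5: mean IRR (p < 0.05) |
|---|---|---|
| Per resident | 1.29 (83%) | 1.15 (37%) |
| Offset: log children assessed | 1.00 (5%) | 0.89 (41%) |

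The offset removes the distortion only when newly examined children resemble those already examined. Otherwise it turns a spurious increase into a spurious decrease.

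**The case against.** **The article is silent on an offset, and an unseen analysis plan may supply one.** This is fair: silence does not establish that the model has no exposure term. But the article does fix the outcome as recorded episodes, the effect measure as an incidence rate ratio and the population as all residents. Resident child-time as exposure, the natural choice given that population, leaves the mixing intact.

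**Detection is an aim of the trial.** The research questions ask about surveillance and detection as well as management. This stands: more recorded episodes per resident is a legitimate result, provided it carries that name. It is not evidence about prevalence.

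**Rate of appropriate antibiotic use for a named diagnosis may mean per diagnosed case.** This also stands in part, and such a denominator would remove most of the volume effect. However, Rates states none and refers back to the approach used for counts, whereas Proportions does condition on having otitis media or hearing loss when it defines the management-plan outcome. A reader might infer that unchanged prescribing would appear as a 30% gain. That follows only on the per-resident reading with y = 1, and the text does not settle the reading.

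**The yield may be low.** Table 4 (item 6) describes usual care as assessment of children who present to the clinic, plus school screening, so children found by outreach could have fewer episodes. Against this, Primary health care workforce reports tympanometry in under 5% of scheduled visits, and HfLI supplies it, so detection per examination may rise. The protocol settles neither point.

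**The protocol concedes limited power for clinical outcomes and will report the proportion receiving services.** The first concerns precision, not bias. The second gives context but adjusts nothing.

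**Conclusion.** The point holds for the episode outcomes: followed as written, the IRR mixes detection with disease and cannot test the hypothesis of less otitis media. At the planning values with disease unchanged, it is expected to be 1.30, 1.15 or 1.08 at full, half or quarter yield. For antibiotics and referral the point holds if they are analysed as counts per resident, which the wording implies but does not state.

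A reader might infer that a successful HfLI will necessarily appear harmful, or that a real benefit will vanish. The documents do not support that. A true 20% fall shows as 1.04 at full yield but 0.92 at half yield, and a fall above 23% gives an IRR below 1 even at full yield. The sizes rest on the assumed yield and on the planning proportions, of which the control value comes from children under 5. They ignore repeat examinations of the same child, which would add to recorded counts.

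Severity is should-fix. The primary outcome, the sample size and the randomisation are not affected.

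**What to change.** 1. Label episodes per resident child as a detection (recorded-episode) outcome. State that its ratio will not be interpreted as incidence, or as evidence of harm or benefit on otitis media.
2. Analyse appropriate antibiotic use and specialist referral as proportions of diagnosed episodes with the indication, in line with the management-plan outcome under Proportions.
3. Report otitis media category among children examined in each period, using the mixed model planned for the primary outcome, adjusted for age and guideline priority group. Present it as conditional on examination.

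**Cost.** Changes to analysis wording; the ear data are already to be extracted every 6 months for all 18 communities.

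**Downside.** Items 2 and 3 condition on something HfLI changes. Children examined under HfLI may differ from those examined under control, and diagnosed cases may shift towards screen-detected disease. The estimate in item 3 can be biased in HfLI's favour (about 0.89 at half yield with no true effect), and adjustment for age and priority group may not remove this. An examination offset alone has the same weakness and should not be presented as a correction.

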##### Subgroup analyses

There may be possibilities of differences in characteristics of populations across the 18 communities during the study period that may confound with the effect of the HfLI. In subgroup analysis, we will adjust for age, sex and factors associated with socio-economic disadvantage in Indigenous children. The subgroup analysis will be carried out as either a stratified analysis or inclusion of an interaction term between each subgroup variable, HfLI factor and time. In all analysis, statistical significance will be set at 5% significance level (*p* < 0.05). Analysis will be conducted using Stata 15.1 (StataCorp LLC, College Station, TX, USA).

The analysis population will be children 0 to 16 years of age who are resident in the participating community. The proportion of the population that receive services will be reported. There will be no imputation for those not seen. We will report participant flow (clusters and participants) for control and HfLI periods, the number of clusters and participants who were assessed for eligibility, were randomly assigned, received intended treatment, and were analysed for the primary outcome.

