### Trial design

The HfLI is designed as an open cohort stepped-wedge cluster randomised superiority trial. Eighteen communities will be allocated according to a computer-generated randomisation list stratified by community size and location, to one of five (steps) 6-monthly HfLI start dates (Fig. 1, Tables 1 and 2).

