**Fig. 1 Fig1:**
[figure not shown]
Design matrix (actual dates inserted prospectively) with dates (month/year) proposed for unblinding and training commencement

**Table 1 Tab1:** Definitions applied to the Hearing for Learning Initiative SW-CRT (see Fig. 1)

Cluster (unit of randomisation)	18 Northern Territory Aboriginal communities (clusters) allocated 2:4:4:4:4 to 5 start dates (sequences). Stratified by NT region (Top End or Central) and size (large or small)
Cluster period (a grouping of observations by time of measurement and cluster)	7 including baseline (i.e. 1 baseline, 5 training or transitions, and 6 Initiatives). Each cluster period has a duration of 6 months
Number of sequences	5 sequences. The order of sequence is 0111111, 0011111, 0001111, 0000111 and 0000011 (0 = control and 1 = initiative)
Number of clusters randomised to each sequence	Variable (2 in 1 sequence and 4 in 4 sequences)
Number of time periods	7 including baseline
Duration of time between each step	6 months
Transition period	3-month training period

**Table 2 Tab2:** Participant timeline (actual dates to be inserted prospectively)

Community numbers	Unblind	Lead-in phase (within control periods)	Cross-over dates (transition periods)	Integration and employment commences (intervention periods)
1–2	Month 1 TP 1	Months 1 to 10* TP1-2	Months 10 to 12 TP2	Month 1 TP3
3–6	Month 10* TP2	Months 10 TP2 to month 4 TP3	Months 4 to 6 TP3	Month 7 TP4
7–10	Month 4 TP3	Months 4 to 10 TP4	Months 10 to 12 TP4	Month 1 TP5
11–14	Month 10 TP4	Month 10 TP4 to month 4 TP5	Months 4 to 6 TP5	Month 7 TP6
15–18	Month 4 TP5	Months 4 to 10 TP6	Months 10 to 12 TP6	Month 1 TP7

*Anticipated delay due to COVID-19 ** TP: 6-monthly TimePeriod (Fig 1)

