### Methods: assignment of interventions (for controlled trials)

#### Allocation sequence generation

Communities will be randomly grouped into two stratification factors—region (Central vs. Top End) and size (small vs. large). These will be further assigned randomly into five different 6-monthly HfLI start dates with transition from control to HfLI being in sequences 0111111, 0011111, 0001111, 0000111 and 0000011 (0 = control and 1 = HfLI).

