#### Dissemination policy

Trial results will be available after data collection from all 18 randomised communities has been completed and analysed, possibly towards late 2023. The results will be reported in aggregate to all communities in the form of clear summaries in plain English, along with recommendations, implications for policy and practice and future directions. Sensitivity analyses according to stratification (Top End and Central, community size large or small) will also be reported. Communities may request information specific to their community, but identification will not be revealed in the aggregate data. Authorship eligibility guidelines set out by the ICMJE will be followed. There are no plans to make public access to the full protocol, participant-level data or statistical code.

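### One of the two routes for subgroup analysis is a subgroup-by-HfLI-by-time interaction, which tests drift rather than effect modification and has no contrast in three of seven periods; the adjustment for confounding is also placed under subgroup analysis

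*Protocol article*

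**What the plan says.** The protocol article, under Subgroup analyses in Statistical methods, offers two routes: an analysis by stratum, or "inclusion of an interaction term between each subgroup variable, HfLI factor and time". The subgroups are listed under Secondary outcomes (integration and employment): three child age groups (0 to 3, 4 to 5, over 5) and the five Priority groups of the 2020 guideline.

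The primary model, under Primary outcome in Statistical methods, has HfLI status and categorical time as fixed effects, with a random cluster intercept and a random coefficient for time. The model for rates also makes time categorical.

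Allocation sequence generation gives "sequences 0111111, 0011111, 0001111, 0000111 and 0000011 (0 = control and 1 = HfLI", and Table 1 says that the 18 communities are "allocated 2:4:4:4:4 to 5 start dates (sequences".

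On covariates, Subgroup analyses first says that differences between community populations may confound the HfLI effect, and then: "In subgroup analysis, we will adjust for age, sex and factors associated with socio-economic disadvantage in Indigenous children". Randomisation used a "computer-generated randomisation list stratified by community size and location". The strata come back in the analysis only under Dissemination policy: "Sensitivity analyses according to stratification (Top End and Central, community size large or small) will also be reported".

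**The concern.** There are two separate problems in one short section.

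**The interaction term.** Whether the HfLI effect differs between subgroups is a question about subgroup by HfLI. Adding time to the product changes the question to whether that difference drifts over calendar time. In a stepped wedge there is a further difficulty. A period-specific HfLI effect needs control and HfLI communities in the same period, and the first and last periods of this design do not have both. An analyst who follows the text literally gets several period-specific interactions, some of them dropped by the software, and no single subgroup result.

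**The adjustment.** Confounding of the HfLI effect is a concern about the effect model. Adjusting within subgroup analyses leaves the main estimate as it was, so the stated remedy does not meet the stated concern.

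At stake are the interpretability of the subgroup results and the coherence of the adjustment plan.

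**Working it through.** **Inputs.** Five sequences over seven periods (Allocation sequence generation); 2, 4, 4, 4 and 4 communities per sequence (Table 1); control proportion 0.329, difference 0.10, two-sided 5%, 90 children per community-period, ICC 0.06, CAC 0.7 (Sample size). No value is given for the individual autocorrelation (IAC), so a range is assumed.

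**Step 1: reproduce the plan's figure.** With J a 7 × 7 matrix of ones and I the identity, the covariance of a community's seven period means is

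V = σ²{ICC[CAC·J + (1 − CAC)·I] + ((1 − ICC)/m)[IAC·J + (1 − IAC)·I]}.

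The variance of the HfLI effect is the matching diagonal element of (Σ XᵀV⁻¹X)⁻¹, where X holds seven period indicators and HfLI. Power is Φ(0.10/SE − 1.96). Take m = 90 and σ² = (0.329 × 0.671 + 0.429 × 0.571)/2 = 0.233.

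| IAC | SE | Power |
|---|---|---|
| 0 | 0.0267 | 96.3% |
| 0.5 | 0.0243 | 98.5% |
| 0.9 | 0.0221 | 99.5% |

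The stated 98% is reproduced within 2 points, so the design has been read correctly.

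**Step 2: where is there a concurrent contrast?**

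| Period | 1 | 2 | 3 | 4 | 5 | 6 | 7 |
|---|---|---|---|---|---|---|---|
| Control communities | 18 | 16 | 12 | 8 | 4 | 0 | 0 |
| HfLI communities | 0 | 2 | 6 | 10 | 14 | 18 | 18 |

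Periods 1, 6 and 7 have none. Table 2 times the start differently: its column headed "Integration and employment commences (intervention periods" runs from TP3 for the first group to TP7 for the last. On that timing the periods without a contrast are 1, 2 and 7, again three of seven.

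**Step 3: rank of the fixed effects, for a two-level subgroup.**

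| Model | Columns | Rank |
|---|---|---|
| Period, subgroup × period, HfLI × period, subgroup × HfLI × period (time categorical) | 28 | 22 |
| Period, subgroup × period, HfLI, subgroup × HfLI | 16 | 16 |
| As the second row, plus HfLI × linear time and subgroup × HfLI × linear time | 18 | 18 |

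The shortfall of 6 in the first row is two effects (HfLI, and subgroup by HfLI) in each of three periods.

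**Step 4: what the four estimable periods give.** Assume two equal subgroups of 45 children who share the community effects. These effects cancel in the subgroup difference, whose covariance is (2σ²(1 − ICC)/45)[IAC·J + (1 − IAC)·I]. With σ² = 0.235 the leading factor is 2 × 0.235 × 0.94/45 = 0.00982. At IAC 0 the period 4 SE is √(0.00982 × (1/8 + 1/10)) = 0.047, and the period 2 SE is √(0.00982 × (1/16 + 1/2)) = 0.074.

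| IAC | SE, single subgroup × HfLI term | SE, period-specific terms (periods 2 to 5) | Ratio |
|---|---|---|---|
| 0 | 0.0271 | 0.047 to 0.074 | 1.7 to 2.7 |
| 0.5 | 0.0228 | 0.036 to 0.056 | 1.6 to 2.5 |
| 0.8 | 0.0147 | 0.023 to 0.036 | 1.6 to 2.4 |

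**Step 5: does leaving region and size out cost precision?** Add both as fixed effects under 300 random placements of 4 Central and 7 large communities among the 18 (illustrative counts; Table 3 lists 20 communities, including two pilots). Use m = 90, IAC 0.5, σ² = 0.379 × 0.621 = 0.235, and hold the variance components fixed. The SE goes from 0.0244 to between 0.0244 and 0.0246, so there is no gain.

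**The case against.** **The three-way term is only an option.** A reader might infer that all subgroup effects will be tested with it. The text says either a stratified analysis or the interaction, and the stratified route avoids the rank problem. Age strata keep all 18 communities. With 30 children per community-period, an illustrative third of 90, the within-stratum SE is about 0.023 to 0.035 for IAC 0.9 to 0, or roughly 82% to 99% power for 10 points. This stands. But separate estimates are not a test of difference, and leaving the choice open allows it to be made after the data are seen.

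**Non-estimability is conditional.** It needs categorical time to carry over from the primary model into the interaction, which the subgroup text does not say. With time linear in the interaction the model has full rank, and with categorical time it can still be fitted with the aliased terms dropped. This also stands, but in both cases the term still addresses drift.

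**The wording may be loose.** It could be shorthand for subgroup by HfLI plus subgroup by time, with details left to an analysis plan. That is possible, but what is written is one interaction among three factors, and it should not be carried forward as it stands.

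**The regional strata.** A reader might infer that a separate Central-only fit is planned and would be too weak to use. Region is not among the listed subgroups. The Dissemination policy section calls the regional results sensitivity analyses and does not specify a separate model, so no power claim about such a fit belongs here.

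**The primary model.** A reader might infer that the primary estimate is wrong without age, region and size. The documents do not support that. An unadjusted primary model is not an error in itself. The random cluster intercept absorbs stable community differences, and the period effects absorb age shifts common to all communities. Only age drift that differs between communities and lines up with crossover could bias the estimate, and nothing in the article shows it.

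**Conclusion.** The point holds in limited form. The three-way interaction is the wrong term for a subgroup test however time is coded. With categorical time its period-specific effects are also not estimable in three of seven periods (rank 22 of 28), and this is true under both the stated sequences and the Table 2 timing. In the remaining four periods each interaction has an SE about 1.6 to 2.7 times that of a single subgroup-by-HfLI term, assuming two equal subgroups of 45 and IAC between 0 and 0.8. The stratified alternative is workable for child-level subgroups but supplies no test of difference.

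The adjustment for confounding sits in an analysis that cannot deliver it. That is a fault in where the remedy is placed, not evidence that the primary estimate is biased. The case for adding age group and the strata rests on consistency with the stratified randomisation and protection against differential age drift in an open cohort. It does not rest on precision.

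**What to change.** 1. In Subgroup analyses, replace the either/or with one model per subgroup variable, fitted in all communities, that contains period, subgroup by period, HfLI and subgroup by HfLI. Name the subgroup-by-HfLI term as the single test. Stratum-specific estimates can be reported from that model.
2. Delete the three-way term. If drift of the effect over time is of interest, specify it as a separate exploratory analysis with its own time coding.
3. Move the covariate adjustment out of the subgroup text and into the analysis of the HfLI effect, with child age group (0 to 3, 4 to 5, over 5), region and size as fixed effects. State whether this adjusted model is primary or supportive.

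The cost is wording in the protocol or analysis plan, before outcome data are analysed. Age, region and size are already recorded, and no change to design, data collection or sample size follows.
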